### Study setting

2.2

This study will be conducted across more than ten hospitals in Guangxi, China, a region with a high incidence of HCC.

### Coordinating center and trial governance

2.3

This trial has received ethical approval from the Ethics Committee of Guangxi Medical University Cancer Hospital (Approval No. CS2025 (115)) and additional participating centers, including the Ethics Committee of the Second Affiliated Hospital of Guangxi Medical University (Approval No. 2025-KYC (0562)), the Ethics Committee of Liuzhou People's Hospital (Approval No. KY2026-030-01) and the Ethics Committee of First People's Hospital of Nanning (Approval No. YJ2025-019). The study is conducted in accordance with the principles of the Declaration of Helsinki, Good Clinical Practice (GCP) guidelines, and all applicable Chinese laws and regulations governing pharmaceutical research and data protection.

### Recruitment

2.4

Eligible patients will be consecutively enrolled from participating centers. All participants will receive comprehensive information regarding the potential benefits and risks of the study interventions to support informed participation and sustained recruitment.

### Informed consent

2.5

Written informed consent will be obtained from each participant or their legally authorized representative prior to initiation of any study-specific procedures. Participants will be fully informed of the study objectives, procedures, potential risks and benefits, alternative treatment options, data confidentiality measures, and their right to withdraw at any time. Adequate time will be provided for questions and consideration. The investigator or designated study personnel will document consent by signature and date, retain the original signed form at the study site, and provide a copy to the participant.

### Patients

2.6

Following hepatic angiography confirming the absence of intrahepatic tumor staining, eligible participants will be randomly assigned in a 1:1 ratio to either the adjuvant TACE group or the intensive follow-up group. In the adjuvant TACE group, participants will undergo a single session of TACE after confirmation of no tumor staining on hepatic arteriography, followed by standardized intensive follow-up. Participants allocated to the intensive follow-up group will receive routine surveillance only after hepatic angiography. Patients in both groups were followed until death or study termination. Key landmarks defining follow-up cessation included: disease progression (defined as HCC recurrence or metastasis), death, withdrawal of informed consent, initiation of a new antitumor therapy, or any other protocol-specified reason for treatment discontinuation.

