### Objectives

2.1

This study is a multicenter phase III RCT, aims to rigorously evaluate the clinical efficacy of adjuvant TACE of HCC patients with high-risk recurrence factors following curative hepatectomy. The primary endpoint of this study is to investigate whether adjuvant TACE could improve RFS in high-risk HCC patients following curative hepatectomy. The key secondary endpoints include the safety and tolerability of adjuvant TACE—such as incidence of treatment-related adverse events (TRAEs) and serious adverse events (SAEs), and the rate of treatment discontinuation attributable to TRAEs or SAEs—as well as the effects of adjuvant TACE versus intensive follow-up on OS, median RFS, and time to tumor recurrence.

RFS is defined as the interval from randomization to the first imaging-confirmed recurrence of HCC—whether intrahepatic or extrahepatic—or death from any cause. TRAEs is defined as any unfavorable or unintended medical occurrences following informed consent, irrespective of causality. SAEs is defined as events that result in death, are life-threatening, require hospitalization or prolong hospitalization, result in persistent or significant disability, cause congenital anomalies, or represent other medically significant conditions. OS is defined as the time from randomization to death from any cause; time to recurrence, defined as the interval from curative hepatectomy to first imaging-confirmed recurrence.

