### Follow-up procedure

2.11

Participants allocated to the adjuvant TACE group will receive a single TACE procedure following hepatic angiography, followed by standardized intensive follow-up, whereas those in the intensive follow-up group will undergo surveillance alone after angiography. Follow-up assessments will be conducted every 3 months (±7 days) from the time of first intervention, and every 6 months (±7 days) after 2 years. At each visit, participants will undergo comprehensive evaluation, including contrast-enhanced CT or MRI of the chest and upper abdomen, measurement of tumor markers such as alpha-fetoprotein and abnormal prothrombin, and additional assessments as detailed in Table 1.

**Table 1 tbl1:** Schedule of study assessments and study timeline.

Phase	Screening period	TACE treatment period	Safety Visit o	Survival Visit p
		C1/D1		
Days	−28∼-1	1	30 days Post-TACE	Every 90 days
Time Window (Days)	NA	+3	±7	±7

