### Sample size calculation

2.12

Sample size estimation was performed using PASS 2021 (version 21.0.3) for a noninferiority randomized controlled trial. Based on historical data from our center, the median RFS for patients with high-risk recurrence factors managed with intensive follow-up alone was 16.1 months,^13^ corresponding to a hazard rate of 0.043 (ln(2)/16.1). Enrollment is planned over 1 year, followed by at least 2 years of follow-up. With a one-sided α of 0.025, 80% power, and a 1:1 allocation ratio, 192 participants per group (total *n* = 384) are required to demonstrate noninferiority at a hazard ratio margin of 1.4, with an estimated 139 events per group. Assuming an annual attrition rate of 5%, an additional 58 participants are required, yielding a total sample size of 442.

Sensitivity analysis was conducted using an alternative median RFS of 19.0 months derived from a cohort excluding DSA-positive patients,^34^ corresponding to a hazard rate of 0.0365 (ln(2)/19.0). Under similar assumptions, 360 and 361 participants would be required in the experimental and control groups, respectively (total *n* = 721), to achieve 80% power at the same noninferiority margin. Given the practical constraints of an investigator-initiated study without commercial funding, enrollment of more than 700 participants is not feasible; therefore, a target sample size of at least 442 participants has been selected to ensure study reliability.

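### Follow-up is worded differently for the two arms, and some assessment dates are tied to a treatment that controls never receive; state one common surveillance plan

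*Protocol article*

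**What the plan says.** Section 2.6 (Patients) describes the arms in consecutive sentences. In the TACE arm, "participants will undergo a single session of TACE after confirmation of no tumor staining on hepatic arteriography, followed by standardized intensive follow-up". The next sentence reads "Participants allocated to the intensive follow-up group will receive routine surveillance only after hepatic angiography". The first sentence of 2.11 (Follow-up procedure) makes the same contrast: standardized intensive follow-up after TACE, "whereas those in the intensive follow-up group will undergo surveillance alone after angiography".

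Other sections name the comparator differently. Objectives (2.1) refers to "the effects of adjuvant TACE versus intensive follow-up on OS, median RFS, and time to tumor recurrence". The sizing (2.12) rests on historical patients: "the median RFS for patients with high-risk recurrence factors managed with intensive follow-up alone was 16.1 months".

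The rest of 2.11 does not split by arm: "Follow-up assessments will be conducted every 3 months (±7 days) from the time of first intervention, and every 6 months (±7 days) after 2 years", and "At each visit, participants will undergo comprehensive evaluation, including contrast-enhanced CT or MRI of the chest and upper abdomen". Table 1 is also a single schedule, but its safety visit, where follow-up imaging is ticked, is timed at 30 days after TACE. Note o counts from TACE, and note p starts the survival visits after that safety visit. Note n starts tumor imaging when investigational treatment is first given.

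**The concern.** The group called intensive follow-up is the one said to receive routine surveillance, while the word intensive is attached to the TACE arm. Read literally, the arms differ in surveillance as well as in TACE. The contrast appears in both sections that define what each arm receives, so it is unlikely to be a single slip.

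This matters because RFS (2.1) runs from randomization to the first imaging-confirmed recurrence or death. A recurrence is dated when a scan shows it. If controls were scanned less often, or from a later start, their recurrences would be found later, their RFS would look longer, and the hazard ratio (TACE over control) would move above 1 with no true effect. That shift is also in the direction of the hypothesis in the Discussion, that TACE adds nothing once resection is truly curative, so the ambiguity would invite challenge to the result.

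**Working it through.** **1. The text, side by side**

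| Place | TACE arm | Control arm |
|---|---|---|
| 2.6 | TACE, then standardized intensive follow-up | routine surveillance only |
| 2.11, first sentence | TACE, then standardized intensive follow-up | surveillance alone |
| 2.1 | adjuvant TACE | intensive follow-up |
| 2.12, source of the control median | not applicable | intensive follow-up alone |
| 2.11, remainder | every 3 months, every 6 months after 2 years | the same, not split by arm |
| Table 1, safety visit with imaging | 30 days after TACE | no TACE to count from |
| Table 1, note n | from first investigational treatment | no such treatment |

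The words only and alone can mean without TACE. That reading does not explain why routine replaces standardized intensive. The single calendar in 2.11 points to equal follow-up. Its origin, the first intervention, is not defined for controls; it could be the angiography, but the text does not say so.

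**2. Does the sizing depend on this?** Inputs from 2.12: margin 1.4, one-sided alpha 0.025, power 80%, 1:1 allocation, control median 16.1 months, 12 months of accrual and 24 months of further follow-up.

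- Events (Schoenfeld) = 4(1.960 + 0.842)² / (ln 1.4)² = 277.3, rounded up to 278, or 139 per arm as stated.
- Hazard h = ln 2 / 16.1 = 0.04305 per month.
- Event probability = 1 − [exp(−24h) − exp(−36h)] / (12h) = 0.722.
- N = 278 / 0.722 = 385, against the stated 384; 192 × 0.722 = 138.6 events per arm.

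The plan's figures reproduce, and none takes the follow-up wording as an input. With one follow-up for both arms they stay at 278 events, 384 participants, and 384 + 58 = 442.

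**3. What unequal scanning would do (illustration only)**

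Assume a true hazard ratio of 1, exponential RFS with median 16.1 months in both arms, every event found at the next scan, and censoring uniform between 24 and 36 months. With scan interval k and censoring time c, let m = floor(c/k).

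- Events detected = 1 − exp(−hkm).
- Person-time = k[1 − exp(−hkm)] / [1 − exp(−hk)] + (c − km)exp(−hkm).

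Averaged over c:

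| Scan interval | Events per patient | Months per patient | Rate per month |
|---|---|---|---|
| 1.5 months (about 6 weeks) | 0.7130 | 17.318 | 0.04117 |
| 3 months | 0.7038 | 17.869 | 0.03938 |
| 6 months | 0.6847 | 18.991 | 0.03605 |

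Apparent hazard ratio, TACE over control:

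- 3-monthly versus 6-monthly: 0.03938 / 0.03605 = 1.09.
- 6-weekly versus 3-monthly: 0.04117 / 0.03938 = 1.05.
- 3-monthly in both arms: 1.00.

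A simulation with a Cox model (15,000 per arm, standard error about 0.014) gave 1.090, 1.046 and 0.995.

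The protocol assigns neither unequal pair by arm. Six-monthly control imaging from the start is an assumption. The 6-weekly case ignores note n's change to 12-weekly after 54 weeks, so it leans high.

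**The case against.** The strongest reply is that the arms already share one plan. Sections 2.1, 2.6, 2.8 and 2.11 all name the control group intensive follow-up. Directly after the disputed sentence, 2.11 gives one calendar and one imaging package without distinction by arm. Table 1 has no lighter control column. Section 2.6 says that patients in both groups were followed to death or study end. Section 2.9.4 keeps participants and investigators blinded, and staff who do not know the allocation cannot run an arm-specific calendar.

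Most of this stands, and it defeats three stronger readings that a reader might draw:

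- That the comparator is not intensive follow-up. No section defines a lighter control schedule, and the contrast can be read as follow-up without TACE.
- That the 16.1-month median no longer describes the control arm. This would follow only if lighter surveillance had actually been prescribed.
- That the plan loses a stated amount of power. Any such figure would rest on interval pairs that the protocol never assigns by arm. It would also rest on the noninferiority test of 2.12, whereas 2.13 describes a superiority framework.

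What the reply leaves open is the dating of control assessments. A shared calendar works only if both arms have a day from which to count. Table 1's imaging visit and note n count from a treatment that controls do not receive. The blinding shows that equal follow-up was probably intended; it does not remove the wording that says otherwise.

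**Conclusion.** The point holds as an inconsistency to be reconciled. Sections 2.6 and 2.11 describe follow-up unequally by arm, against the objective, the sizing source and the calendar later in 2.11, and several Table 1 anchors do not carry over to controls. Unequal detection of recurrence is a risk of literal reading, not something that the protocol sets.

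The size is conditional. The apparent hazard ratio would be about 1.05 to 1.09 against TACE under the assumed unequal intervals, exponential RFS and no true effect, and 1.00 under a shared calendar. The sample size does not change. The point still deserves correction because it touches the dating of the primary endpoint and costs almost nothing to settle.

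**What to change.** Amend 2.6 and the first sentence of 2.11 to say that, after angiography, both arms receive the same follow-up: the same visits, imaging modality and calendar, with TACE the only planned difference. Rewrite the 2.11 origin and the Table 1 safety-visit heading and notes n, o and p so that each assessment is counted from an origin that exists in both arms. Randomization is a natural choice, since RFS already starts there.

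The calendar in 2.11 (every 3 months, every 6 months after 2 years) and the one in note n (every 6 weeks, every 12 weeks after 54 weeks) also disagree. They must be reconciled in the same amendment, and the sponsor decides which interval applies.

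The cost is a few sentences in an amendment and a note to sites, with no additional participants. A site that had planned lighter follow-up for controls would need to perform the visits that 2.11 already schedules for everyone.

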### Strategies to improve adherence to interventions

2.7

The interventions employed align with established clinical practice. Participants in the adjuvant TACE group will receive treatment in accordance with CNLC recommendations,^29^ facilitating early detection of residual disease. Participants in the intensive follow-up group will avoid unnecessary treatment-related costs and potential adverse effects. The study will be conducted in accordance with GCP and applicable ethical standards. Investigators will maintain consistent and thorough communication with participants to promote adherence, reduce loss to follow-up, and minimize missing data. Prior to enrollment, investigators will provide a detailed explanation of study procedures, potential benefits, associated risks, and participant rights, including the right to withdraw consent at any time without consequence. Enrollment will proceed only after written informed consent has been obtained.

All analyses will follow the intention-to-treat principle. Participants who discontinue treatment or withdraw from the study prior to completion of the protocol-specified regimen will be encouraged to continue follow-up and complete all scheduled assessments. At the time of discontinuation or withdrawal, all end-of-treatment evaluations will be performed. For participants who withdraw for reasons other than disease progression, imaging assessments will remain mandatory.

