n Tumor assessments will be conducted in accordance with Response Evaluation Criteria in Solid Tumors version 1.1 (RECIST 1.1)^36^ and modified RECIST (mRECIST).^37^ Imaging evaluations will primarily consist of contrast-enhanced computed tomography (CT) or magnetic resonance imaging (MRI), with mandatory inclusion of thoracic and abdominal regions. At baseline, within 28 days prior to enrollment, additional imaging assessments—including pelvic CT or MRI, cranial MRI, and whole-body bone scan—are required. If cervical lymph node enlargement is present, contrast-enhanced neck CT should also be performed. Positron emission tomography/computed tomography (PET/CT) may be used as a baseline screening modality; if abnormalities are detected, corresponding contrast-enhanced CT or MRI examinations must be performed to facilitate subsequent longitudinal comparisons. For participants without evidence of metastatic disease at baseline, routine cranial, pelvic, and whole-body bone imaging is not required during follow-up unless clinically indicated. Imaging modalities and techniques should remain consistent throughout the study for each participant. Tumor imaging evaluations will be performed every 6 weeks (±7 days) starting from the first administration of investigational treatment, and subsequently every 12 weeks (±7 days) after 54 weeks. Upon the first radiological assessment indicating progressive disease based on RECIST 1.1, participants with clinically stable disease, absence of rapid radiological progression, and investigator-determined potential for continued clinical benefit may continue the current investigational treatment. In such cases, a confirmatory imaging assessment must be performed after a minimum interval of 4 weeks in accordance with RECIST 1.1. If progression is confirmed, the participant must discontinue investigational treatment; if not confirmed, treatment may continue with ongoing imaging evaluations per the protocol-defined schedule until radiologically confirmed progression. For participants who discontinue investigational treatment for reasons other than objective disease progression, tumor imaging assessments must be conducted at the time of treatment discontinuation and continued thereafter according to the protocol-specified schedule until the earliest occurrence of initiation of new antitumor therapy, confirmed disease progression, loss to follow-up, death, or withdrawal of informed consent. Unscheduled imaging assessments may be performed at any time if clinically indicated. In cases of clinically unstable disease following initial radiological progression, confirmatory imaging after 4–6 weeks is not required, and investigational treatment should be discontinued immediately.

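### Section 2.6 follows patients to death yet ends follow-up at recurrence or new antitumor therapy, leaving it unclear how far OS and RFS are ascertained

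*Protocol article*

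**What the plan says.** Two adjacent sentences in section 2.6 (Patients) set the follow-up rule. The first reads "Patients in both groups were followed until death or study termination". The second reads "Key landmarks defining follow-up cessation included: disease progression (defined as HCC recurrence or metastasis), death, withdrawal of informed consent"; it then adds the start of a new antitumor therapy, and it closes with any other protocol-specified reason for stopping treatment. Nothing confines the second sentence to imaging or to treatment.

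Other provisions that bear on the point:

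- **Section 2.1, endpoints.** "OS is defined as the time from randomization to death from any cause". "RFS is defined as the interval from randomization to the first imaging-confirmed recurrence of HCC", or death from any cause. New antitumor therapy is neither an RFS event nor a stated reason for censoring.
- **Section 2.6.3.** Starting antitumor therapy outside the study is a ground for stopping treatment or being withdrawn.
- **Section 2.7.** "All analyses will follow the intention-to-treat principle". Participants who stop early "will be encouraged to continue follow-up and complete all scheduled assessments", and imaging stays compulsory for those who withdraw for reasons other than progression.
- **Table 1, note n.** For participants who stop study treatment without objective progression, imaging runs "until the earliest occurrence of initiation of new antitumor therapy, confirmed disease progression, loss to follow-up, death, or withdrawal of informed consent".
- **Table 1, survival visit column, and note p.** Survival status and subsequent antitumor treatment are recorded. Contact is every 90 days, by visit or telephone, and no stop at recurrence is stated.

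**The concern.** Sites have to act on this text, and section 2.2 expects more than ten hospitals. A site that applies the cessation list stops contact at recurrence. A site that applies the preceding sentence, or note p, does not. Data that were never collected cannot be restored by an analysis plan.

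Two endpoints are exposed in different ways:

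- **OS.** If contact stopped at recurrence, OS would record only deaths without prior recurrence. It could not compare the arms on death from any cause.
- **RFS.** Stopping at recurrence does no harm, because recurrence is the event. The exposure is new antitumor therapy started before imaging-confirmed recurrence. If assessment ends there, the participant is in effect censored at a moment that may well be related to prognosis. An intention-to-treat analysis needs the later scans and deaths.

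**Working it through.** **1. The plan's own figures (section 2.12).** Inputs: control median RFS 16.1 months, accrual 12 months, minimum follow-up 24 months, one-sided alpha 0.025, power 80%, margin 1.4.

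- Events = 4(1.960 + 0.842)² / (ln 1.4)² = 277.3, so 278, or 139 per group, as stated.
- Hazard h = ln 2 / 16.1 = 0.04305 per month.
- Probability of an RFS event by study end = 1 − (e^(−24h) − e^(−36h)) / (12h) = 1 − (0.3558 − 0.2123)/0.5166 = 0.722.
- N = 277.3 / 0.722 = 384, as stated. 384 × 1.15 = 442, as stated.

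**2. OS if the cessation list governed.** Among 442 participants, 442 × 0.722 = 319 RFS events are expected. Let s be the share of first events that are deaths without recurrence. Take survival after recurrence as exponential with median m. Neither s nor m is in the document; I assume s = 5, 10 or 20% and m = 12 to 48 months.

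- Deaths still recorded = 319 × s, which is 16, 32 or 64.
- Deaths after recurrence come from simulating time to recurrence plus time from recurrence to death against a cutoff uniform on 24 to 36 months.

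Total deaths per 442, with the percentage that follow recurrence and would be lost:

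| s | m = 12 | m = 24 | m = 36 | m = 48 |
|---|---|---|---|---|
| 5% | 199 (92.0%) | 135 (88.1%) | 103 (84.5%) | 85 (81.2%) |
| 10% | 206 (84.4%) | 144 (77.8%) | 114 (72.2%) | 97 (67.0%) |
| 20% | 219 (70.8%) | 164 (61.1%) | 137 (53.4%) | 122 (47.5%) |

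Example, s = 20% and m = 48: 57.8 / 121.6 = 47.5%. The lost share exceeds half in 11 of the 12 cells.

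**3. RFS if new therapy before recurrence ended assessment.** Add a constant censoring hazard c to h. Expected events = 442 × h/(h + c) × [1 − (e^(−24(h+c)) − e^(−36(h+c))) / (12(h + c))]. Power = Φ(√(events/4) × ln 1.4 − 1.960), in the noninferiority frame of section 2.12. The 5% annual attrition is the plan's own; the therapy rates are assumptions.

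| Annual rate of new therapy before recurrence | Events | Power |
|---|---|---|
| 0% (attrition only) | 304 | 83% |
| 5% | 289 | 82% |
| 10% | 275 | 80% |
| 20% | 248 | 75% |

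This calculation treats the censoring as independent, so it shows lost information only. The bias from prognosis-related censoring cannot be sized from the document.

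**4. The passages side by side.** For OS, the cessation list stands against the sentence before it, the OS definition, the survival visit column and note p. For RFS, the cessation list and note n both name new therapy as an end point. Against them stand the RFS definition, which is silent on new therapy, and section 2.7, which calls for continued assessment.

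**The case against.** A reader might infer that the plan discards most deaths from OS. The documents do not support that as a statement of fact. The sentence before the list runs to death, and note p schedules contact with no stop at recurrence. Recording subsequent antitumor treatment at the survival visit makes sense only if contact outlasts recurrence or new therapy. The list also ends with reasons for stopping treatment, so it may have been meant for the treatment or imaging phase. This stands, and it makes the OS loss conditional. It does not remove the contradiction, because the sentence says follow-up without qualification.

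A reader might also infer that the primary hazard ratio will be biased. That is too strong as well. No passage states an RFS censoring rule, and such rules are often left to the analysis plan. Exposure is limited: section 2.10 bars antitumor therapy until 120 days after the final intervention, and note n reaches only those who discontinue a treatment given in a single session (section 2.8). What survives is narrower. A stated rule would end data collection at new therapy, and an analysis plan cannot make up for scans not taken.

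Finally, the OS percentages rest on assumed inputs, and in one of the 12 scenarios the lost share falls just below half.

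**Conclusion.** The point holds as an internal contradiction with a conditional consequence for OS and a separate, narrower risk for RFS.

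- **OS.** If the cessation list were followed, about 47 to 92% of deaths would go unrecorded. This rests on an assumed recurrence share of 80 to 95% of first events, an assumed post-recurrence median of 12 to 48 months, and exponential times. Table 1 and note p suggest that this is not the intention.
- **RFS.** Ending assessment at new antitumor therapy before recurrence conflicts with the intention-to-treat statement and the continued-assessment rule. It risks informative censoring of the primary endpoint. Size and direction are unknown; the loss of power alone is modest at the assumed therapy rates. Ending RFS imaging at recurrence itself is harmless.

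**What to change.** Reconcile sections 2.6, 2.6.3 and 2.7 with Table 1 notes n and p, so that each event is tied to the kind of follow-up it ends:

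- Recurrence or metastasis ends RFS imaging only.
- Survival status and subsequent therapy are collected every 90 days, by telephone where needed as note p allows, until death, withdrawal of consent or study end, for every randomised participant.
- New antitumor therapy without recurrence ends neither scheduled imaging nor RFS ascertainment. Later events count in the intention-to-treat analysis, with censoring at new therapy as a sensitivity analysis.
- Remove recurrence and new therapy from the general cessation list in section 2.6, and new therapy from the imaging stop rule in note n.

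The cost is an amendment to wording, plus some continued imaging in participants who start new therapy without recurrence. The 90-day contacts are already scheduled. The change should be made before follow-up data accrue. It concerns data collection only and sets no rule for clinical treatment.
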